#### Other variables

##### Socio-demographic and health profile

For the characterization of the sociodemographic and health profile, a semi-structured questionnaire will be used, composed of information related to age, sex, marital status, race, years of study, retirement, profession, monthly income in the minimum wage (R$ 1,212.00 for 2022) referring the 2010 Demographic Census of the Brazilian Institute of Geography and Statistics (IBGE) for smoking, self-perception of health status, and the number of medications used and morbidities.

##### Pain intensity

Pain intensity will be evaluated by the visual analog scale (VAS), which consists of a widely used instrument [52], with great discrimination power to evaluate individuals with fibromyalgia [53]. VAS is reliable and highly correlated with other forms of pain assessment [54]. It is sensitive to pharmacological and non-pharmacological procedures, which alter the painful experience, and strongly correlates with pain measured by other scales, since it has shown considerable discriminative power for pain detection in individuals with fibromyalgia, with high sensitivity and specificity (80 and 80%, respectively) [53]. This instrument consists of a straight 10-cm line, devoid of numbers, with indications at each end for “absence of pain” and “unbearable pain”. The individual marks on the line the intensity of their pain, which can range from 0 to 10 [55].

##### Sleep quality

For the evaluation of the quality of sleep, the Pittsburg Sleep Quality Index (PSQI) will be used. It is a tool of previously established trustworthiness and validity [56, 57]. Reliability estimates showed internal consistency of 0.83 for the seven component scores and test–retest reliability of 0.85 for the overall PSQI scores [58], presenting good applicability and effectiveness in clinical practice and research [59]. The discriminative power with sensitivity and specificities are considered high (89.6 and 86.5%, respectively) [60]. The instrument was created by Buysse et al. [60]. In its translated version, it was adapted and validated for the Brazilian population by Bertolazzi [61]. It is a self-report tool, which evaluates sleep quality in the last month, through 19 items, distributed between seven components (sleep quality, sleep latency, sleep duration, sleep efficiency, sleep alterations, use of medications for sleep and diurnal dysfunction), graded on a scale of 0 to 3. The sum of the components of the PSQI indicates the overall score, which ranges from 0 to 21. Scores between 0 and 4 suggest good sleep quality, between 5 and 10 indicate poor sleep quality, and above 10 points indicate the presence of a sleep disorder [62].

##### Self-care agency

Self-care agency will be evaluated by the Revised Self-Care Capacity Assessment Scale (R-SCAS), which was developed by Evers [63] and adapted and validated for the Brazilian context by Damásio and Koller [64]. This instrument presents good applicability [65], with an internal consistency classified as positive [66] and satisfactory results of validity and trustworthiness [65, 67]. The R-SCAS presents 15 items that correspond to a 5-point Likert scale, whose score ranges from 1 to 5, and contains statements that can be assigned five response options: (1) strongly disagree; (2) disagree; (3) neither disagree nor agree; (4) agree; (5) strongly agree. The total score of the R-SCAS is obtained by adding the results of the items and ranges from 15 to 75 points. Items 4, 11, 14, and 15 present negative content and their score needs to be reversed to obtain the total score. Higher values indicate greater self-care capacity [64].

##### Use and costs of health services and social assistance

The Client Socio-Demographic and Service Receipt Inventory (CSSRI) was developed in England by Chisholm et al. [68], to be used in economic studies and in studies that evaluate health services. This tool has been widely used in research in European countries and is a useful and reliable tool for this purpose. Since the structure of the health services offered varies in each country and region, local adaptation becomes mandatory. Thus, the CSSRI was translated into Portuguese and adapted to the organizational structure of public health services Brazil by Souza et al. [2]. The trustworthiness between appraisers was excellent as a whole [69–71]. This is a semi-structured inventory, divided into six main topics: (1) Sociodemographic data of users; (2) Living and housing conditions; (3) Use of community or hospital accommodations; (4) Employment and income data; (5) Medication consumption; (6) Use of health, social and criminal services. All information is referred to in a retrospective time period perspective (last month, last 3 months, last 6 months). This tool was adapted for the present study, using only data related to medication consumption and use of health and social services. The costs per unit for each of these services, the procedures performed and the medications consumed will be calculated later, based on the data collected [72].

##### Program feasibility

At the end of the feasibility study period, participants with fibromyalgia and professionals will make an evaluation with the researchers, of a quantitative and qualitative nature, with questions about the experience, themes, duration of the meeting, the performance of the professional, and the limitations encountered during the participation of the program. In addition, participants will also be instructed to record the level of satisfaction with the program using a 10-point Likert scale, where 0 represents totally dissatisfied and 10 represents totally satisfied [73]. Moreover, the expectation and the credibility of the result of the treatment will be evaluated by the Credibility/Expectancy Questionnaire (CEQ). The first and so far one of the most used tools for this variable [74, 75], so named by Devilly and Borkovec [76] and developed from a questionnaire based on, and created by, Borkovec and Nau [77], this tool evaluates the willingness of patients to recommend treatment to other people [75], as well as the expectations of the intervention [78]. The tool was adapted, translated into Portuguese, and used by previous Brazilian studies [79, 80]. Evidence of the good reliability and predictive validity of this measure was provided [76]. The CEQ is a scale divided into two types of questions [74]: four (items 1, 2, 3, and 5), which assess the expectation, that is, what they expect in relation to what the treatment improves (ranging 1 to 9) and two (items 4 and 6) assessing the credibility (ranging 0 to 100%). Both subscales have shown high internal consistency [76, 81]. Everything will be recorded and later analyzed by the physiotherapist responsible for identifying the problems and proposing solutions.

##### Program adhesion

At the end of the program, the participants’ adherence to “Amigos de Fibro (Fibro Friends)” will be verified, using the following parameters: abandonment rate (%) and attendance rate (%). These parameters also allow us to evaluate the viability of the program [73].

##### Qualitative process evaluation

For qualitative data, we will use a semi-structured interview script, composed of questions created by the authors themselves that deal with their participation, perception of the methodology, subjects addressed, and impact on their lives. The data collection process will be carried out individually by the researcher, who will schedule an appointment with each participant. There will also be the same questions for professionals. Data will be obtained through semi-structured interviews, recorded with the consent of the participants. The recordings will be transcribed by a company specialized in shorthand monitoring and audio transcription, providing reliability and faithfully revealing the testimonies of the participants.

Regarding the deadlines for pre and post evaluations, and interventions will be as follows:Pre-assessment: from 1 to 7 days before the intervention.Post-assessment: from 1 to 7 days after the intervention.Intervention: 3 months of intervention.Follow-up: 3, 6, and 12 months after the intervention.

### Participant timeline {13}

The evaluation schedule, interventions, and follow-up are presented in Fig. 4 through a schematic diagram highly recommended in protocol studies.

**Fig. 4 Fig4:**
[figure not shown]
Study timepoints

### Sample size {14}

The sample size was based on the assumptions of group educational interventions, where it is not necessary to formally calculate the sample size due to the characteristics of the intervention [27, 38, 78, 82–84]. The size of the group should consider that the number of participants allows everyone to manifest and feel tended to. The coordinator should feel comfortable with the number of individuals and that the main needs of the participants are being met. Its size cannot exceed the limit that endangers visual and auditory communication [34, 85, 86]. It is recommended that the ideal size of a health education group be a maximum of 12 members [34]. The sample will consist of 24 participants, divided into two groups, with 12 individuals each. Regarding the loss of participants, we will use the intent-to-treat purpose. The present study hopes to obtain quantitative data to use as a basis for future studies of “Amigos de Fibro (Fibro Friends)”.

### Recruitment {15}

Recruitment is carried out through dissemination on the Brazilian Association Fibromyalgia (ABRAFIBRO) social networks, a support network for people seeking information about the syndrome in Brazil. The association has a supportive purpose and it is not possible to calculate the number of people who will receive the message, because social networks are comprehensive and allow the sharing of information. They will also be able to recruit people from rheumatology clinics throughout Brazil (all states); however, there is no exact number of rheumatology clinics in the country. Finally, as extra steps taken to recruit enough people, you may send letters to potential participants known to the research group. The estimated recruitment rate will be 80%.

## Assignment of interventions: allocation

### Sequence generation {16a}

Simple controlled randomization will be performed using Randomized (http://randomized.com), by an independent researcher, who will not be involved in the recruitment and intervention of participants.

### Concealment mechanism {16b}

The allocation will be made secretly, that is, through a numerical sequence, in which there will be a letter on whether the individual will belong to the experimental group (EG) or the control group (GC) [87].

### Implementation {16c}

An independent researcher who is not participating in the other stages of the study will be responsible for managing the allocation sequence, and enrollment of participants and will assign participants to interventions.

## Assignment of interventions: blinding

### Who will be blinded {17a}

Participants will be evaluated pre- and post-intervention by a blind evaluator, previously trained to obtain information and confirm eligibility criteria, in addition to primary and secondary outcomes. The evaluator will be asked to guess which group the participants were in (intervention or control) at the end of the study to measure the blindness of the evaluator. Due to the nature of the interventions, it will not be possible to blind neither the responsible participants nor professionals towards the application of the web-based intervention. Regarding the data analyst, he will be blind to carry out this stage of the study.

### Procedure for unblinding if needed {17b}

We believe that this procedure will not be necessary. If yes, we will take all necessary ethical measures. The circumstances in which the disclosure will be necessary may be as follows: there is a conversation between the participants in which intervention they are in, disclosure of photos or videos of the intervention posted by the participants on social networks, the evaluator for some personal reason revealing which group the participants are in, among other relevant ones.

## Data collection and management

### Plans for assessment and collection of outcomes {18a}

Data will be collected by only one trained person (pre, post, and follow-up) for standardization and to avoid data duplication. The person trained to collect the data is a researcher, with training in physiotherapy and a master’s degree in the area of health promotion. In addition, the person responsible for cleaving the data is not part of the authorship and group of researchers of the study. The instruments used in the study are detailed in the methodology section. All instruments are reliable and validated. If the reader needs a detailed version of the questionnaires, with all the tests, he can request the corresponding author by email and he will receive the file (in addition to the data that are explained in the protocol).

### Plans to promote participant retention and complete follow-up {18b}

After the intervention, the primary and secondary variables of both groups will be collected again, as well as after 3, 6, and 12 months to verify the effect and maintenance of the intervention. The researchers will be in contact with the patients on a monthly basis, sending positive messages on their phones to maintain a bond until the last evaluation.

### Data management {19}

Data will be collected through online forms, through the Google Forms platform. After data collection, participants will be identified by a number and names and private data will not be identified. Soon after, the data will be stored in Microsoft Office Excel (2013) with complete security. Data that are not in the protocol can be found through a direct request with the responsible author. There will be no paper-based data entry, as it will be electronic, as previously mentioned (Google Forms). Other important data management information will be:Simple controlled randomization will be performed using Microsoft Excel 8.0 software for Windows, by an independent researcher, who will not be involved in the recruitment and intervention of participants. The allocation will be made secretly, that is, through a numerical sequence in opaque and sealed envelopes, in which there will be a letter identifying which group the participant will be in.The participants will be evaluated individually pre and post-intervention by the same evaluator who did not know which group the participant belonged to. The evaluator will undergo a one-week training with a total of 15 h, based on the simulated application of the questionnaires, indicated verbal command and possible doubts that could arise during the application. After training, the evaluator will be able to obtain information and confirm the eligibility criteria, in addition to applying the evaluation instruments used.Data organization will also be carried out by an independent researcher.The data will be under the responsibility of the researchers and, if necessary, will be made available without identifying the participants.

### Confidentiality {27}

The study will adhere to the guidelines established by the General Law for the Protection of Personal Data, Law No. privacy. In accordance with the recommendation of the General Law for the Protection of Personal Data, data will be anonymized and password protected. In this context, data will be stored on a password-protected personal computer to prevent damage from occurring as a result of data processing. Participants will receive an individual study identification number. If requested, anonymous study data will be shared with other researchers to allow for prospective international meta-analyses. Also, according to item XI.2.f., of Resolution 466/12, the data will be kept in a digital file, under the custody and responsibility of the researcher, for a period of 5 years after the end of the research and will be available to any clarification of doubts.

### Plans for collection, laboratory evaluation, and storage of biological specimens for genetic or molecular analysis in this trial/future use {33}

There will be no collection of biological samples in the study.

## Statistical methods

### Statistical methods for primary and secondary outcomes {20a}

#### Quantitative analysis

Participant code numbers will ensure blinding of data analysis. Data will be entered into Microsoft Office Excel (2013) and will be used in the descriptive analysis of demographic data. Categorical data will be described using counts and percentages. As recommended, continuous data will be presented using medians and interquartile ranges, whether they be normal or not. Differences between intervention and control groups will be tested using non-parametric tests. A 5% level of significance will be used for all statistical tests. Data analysis will be undertaken in SPSS version 22.

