### Objectives {7}

The primary objective of the “Amigos de Fibro (Fibro Friends)” study is:

To evaluate the effectiveness of a web-based educational intervention associated with physical exercise to promote the health and quality of life of people with fibromyalgia in Brazil.

The secondary objectives are four:To verify the effect of an educational intervention associated with physical exercise via the web on pain intensity, sleep quality, and self-care management in patients with fibromyalgia.Measure the use and costs of social and health care services and the feasibility of a web-based educational intervention associated with physical exercise aimed at patients with fibromyalgia.To identify the adherence of individuals with fibromyalgia participating in an educational program associated with physical exercise to promote health via the web.Evaluate the maintenance of results obtained in individuals participating in an educational program associated with physical exercise for health promotion via the web in the short, medium, and long term.

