### Methods for additional analyses (e.g., subgroup analyses) {20b}

There will be no further analysis. The analyses carried out are described in the study.

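### The analysis plan sets medians, IQRs and rank-type tests for all continuous data with no exception for costs, so as written it yields no mean cost or mean cost difference and only indirect planning inputs for later trials

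*Protocol article*

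**What the plan says.** Under Statistical methods for primary and secondary outcomes {20a}, Quantitative analysis, the article sets one summary for all continuous data: "continuous data will be presented using medians and interquartile ranges, whether they be normal or not". The comparison is equally general: "Differences between intervention and control groups will be tested using non-parametric tests". The only other specification is that "A 5% level of significance will be used for all statistical tests". The section names no mean, SD, effect estimate or confidence interval.

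Costs belong to the outcomes that this section covers. The Abstract lists use and costs of health and social care services among the secondary outcomes, and Objectives {7} includes this aim: "Measure the use and costs of social and health care services and the feasibility of a web-based educational intervention". The outcome section on use and costs says how costs will be derived ("The costs per unit for each of these services, the procedures performed and the medications consumed will be calculated later, based on the data collected") but gives no separate summary or comparison for them.

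Sample size {14} makes no formal calculation and sets 24 participants, 12 per arm. It adds: "The present study hopes to obtain quantitative data to use as a basis for future studies".

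**The concern.** The rule is a stated choice, applied whatever the distribution. It fits two of the trial's own aims poorly.

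**Costs.** What a service spends is the arithmetic mean cost times the number treated. A median does not give that total, and a rank test does not test a difference in it. Costs are often right-skewed, with a few heavy users carrying much of the total. Those users barely move a median, so two arms with different total cost can show the same one.

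**Later studies.** A trial on the FIQ or a similar scale is usually sized from a mean difference, an SD and, if baseline adjustment is planned, the baseline-to-follow-up correlation. Medians, IQRs and p-values give an SD only by approximation and do not give the correlation.

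**Working it through.** **Inputs from the protocol article.** 12 per arm (Sample size {14}); 5% significance level, median and IQR, non-parametric tests (Quantitative analysis). The documents give no SD, no cost distribution and no proportion of non-users. All distributions below are therefore assumed, and ranges are shown. Tests are taken as two-sided, also an assumption. The figure of 24 participants comes from the maximum size of an education group, so there is no power calculation to reproduce.

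**1. What 12 per arm can detect.** At two-sided 5% and 80% power, the detectable standardised difference is about 1.14 (normal approximation) or 1.20 (t test). Only very large effects would be found reliably, so estimates for later planning are a main quantitative product of the trial.

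**2. Mean against median cost.** For log-normal costs with log-SD s, mean/median = exp(s²/2).
- s = 0.5: exp(0.125) = 1.13
- s = 1.0: exp(0.5) = 1.65
- s = 1.5: exp(1.125) = 3.08

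**3. Non-users.** With 12 in an arm, the median is the average of the 6th and 7th ordered values. If 7 or more do not use a service, both values are 0 and the median cost is 0, whatever the other participants cost. If exactly 6 do not use it, the median is half the smallest positive cost. The statement therefore needs more than half of the arm to be non-users.

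**4. Rank test with equal medians and unequal means.** Mann-Whitney was simulated at 12 per arm with log-normal costs, equal medians and 20,000 runs. The ratio of means is exp((s₂² − s₁²)/2).
- s = 0.8 v 1.2: exp((1.44 − 0.64)/2) = 1.49; rejection in 4.8% of runs
- s = 0.5 v 1.5: exp((2.25 − 0.25)/2) = 2.72; rejection in 6.1% of runs

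Both rejection rates are close to the nominal 5%. The test responds to a different quantity.

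**5. Recovering an SD from the reported IQR.** For normal data an SD can be approximated as IQR/1.35. With n = 12, true SD 1 and 200,000 runs:

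| Source of SD | CV | 95% range | Later N relative to the right N (SD²) |
|---|---|---|---|
| Reported SD | 21% | 0.59 to 1.41 | 0.35 to 1.99 |
| IQR/1.35 | 30% | 0.52 to 1.76 | 0.27 to 3.11 |

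For roughly symmetric scores this is a loss of precision and no more. For log-normal costs (median 1) the approximation fails. The true SD is √[(exp(s²) − 1)·exp(s²)] and the IQR is exp(0.6745s) − exp(−0.6745s).
- s = 0.5: 0.60 against 0.51, a ratio of 1.19; N understated 1.4-fold
- s = 1.0: 2.16 against 1.08, a ratio of 2.01; N understated 4.0-fold
- s = 1.5: 8.97 against 1.77, a ratio of 5.08; N understated 25.8-fold

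**6. Does the obvious remedy work at this size?** A nominal 95% bias-corrected bootstrap interval for the mean cost difference was simulated at 12 per arm (2,000 runs, 1,000 resamples). Coverage was about 88% (s = 1.0 in both arms), 87% (1.5 in both), 83% (0.8 v 1.2) and 74% (0.5 v 1.5). The interval is informative, but it is not a 95% interval.

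**The case against.** **The rule may not reach costs, and an unseen analysis plan may fill the gap.** The Quantitative analysis section does not mention costs and does not forbid means. The sentence under Methods for additional analyses {20b}, "There will be no further analysis. The analyses carried out are described in the study", can be read as ruling out subgroup analyses rather than extra table columns. This stands in part: that only medians will appear is an inference. But the section is headed for primary and secondary outcomes, costs are one of these, and no exception is written. The point is directed at a method that the article states, not at missing detail.

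**Medians and rank tests are sound at 12 per arm.** This stands in full, and the fix keeps them.

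**The aims are worded modestly.** A reader might infer that the plan cannot answer its cost objective. The documents do not support that. The objective is to measure use and costs, which counts, percentages and medians describe in part, and no budget impact or mean cost difference is promised. Nor does Practical implications promise primary-care managers a cost figure.

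**Later studies are not left empty-handed.** A reader might also infer that the trial can give no planning inputs. That is too strong. An SD for roughly symmetric scores can be approximated from the IQR, attendance and abandonment rates will be reported (Program adhesion), and anonymised data are offered on request (Confidentiality {27}; {31c}; Data Availability). Data on request, however, are not a planned result of the trial's own report.

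**The size is assumed.** This also stands. No cost spread is given, and the zero median applies to single services. The article says that these patients use health services more than others, so a zero median total cost is not implied.

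**Conclusion.** The point holds as a mismatch between one blanket rule and two of the trial's aims, and should be corrected. As written, the plan gives no mean cost and no mean cost difference, and its tests do not address one. For the four scales it gives later planners an SD only by approximation (CV about 30% instead of 21%) and no correlation. Under assumed log-normal costs the mean is about 1.1 to 3.1 times the median, and a 1.5- to 2.7-fold difference in means with equal medians goes almost unnoticed by a rank test. These sizes depend on the assumed distributions. The structural point, that a median and a rank test do not estimate a mean cost, does not.

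**What to change.** In Quantitative analysis, keep the medians, IQRs and non-parametric tests, and add two items:

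- **Costs:** the arithmetic mean and SD per arm, and the between-arm mean difference with a bootstrap 95% CI. Label the interval descriptive, and state that its coverage falls below 95% with skewed data at 12 per arm (about 74-88% under the log-normals assumed here).
- **FIQ, pain VAS, PSQI and R-SCAS:** the mean, SD, baseline-to-follow-up correlation and between-arm difference with 95% CI.

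This needs no new data or visits, only a few more table columns. The intervals will be wide and approximate, which anyone planning from these figures needs to see.

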#### Main outcome variable

##### Quality of life

The Fibromyalgia Impact Questionnaire (FIQ) was first developed by Burckardt, Clark, and Bennett [46], and translated and adapted to the Brazilian population by Marques et al. [47], reviewed by Bennett et al. [48] and validated for Brazil by Paiva et al. [49] will be used. This tool has been demonstrated to be trustworthy and valid. The FIQ is a change-sensitive and clinically measurable tool [50], which has good discriminative power, with high sensitivity and specificities (78.2 and 81.2%, respectively) [51]. Other aspects of these tools are also important, such as applicability, practicality, and clarity [50]. This tool consists of 19 questions, organized into 10 items: functional capacity, well-being, work absences, workability, pain, fatigue, morning tiredness, stiffness, anxiety, and depression [47]. Item 1’s value can range from 0 to 30, and items 2 and 3’s values can range from 0 to 7. The remaining items are composed of visual analog scales ranging from 0 to 10. To obtain the tool’s score, item 2 must be recorded (0–7, 1–6, 2 = 5, 3 = 4, 4 = 3, 5 = 2, 6 = 1, and 7 = 0) and normalized on a scale of 0 to 10. Items 1 and 2 must also be normalized, so that all the items are expressed in similar units [47]. The total FIQ score will be obtained by the sum of the items, ranging from 0 to 100. The highest values indicate a greater impact of fibromyalgia in quality of life. The total score will also classify impairment as mild (0 to 38) or severe (59 to 100) [47].

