### Methods in analysis to handle protocol non-adherence and any statistical methods to handle missing data {20c}

In case of non-adherence of the participants, the intention-to-treat method will be used. The intent-to-treat method is a statistical approach used in clinical trials and experimental studies to analyze outcomes regardless of compliance with the original protocol. The principle of the intention-to-treat method is that participants should be analyzed according to the group to which they were initially assigned, regardless of whether or not they followed the treatment as planned.

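### The stated analysis makes no use of baseline FIQ, and intention-to-treat, the only rule for losses and missing data, fixes a participant's arm but supplies no outcome value

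*Protocol article*

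**What the plan says.** The primary outcome is the FIQ total: "The total FIQ score will be obtained by the sum of the items, ranging from 0 to 100" (Quality of life). Under Outcomes {12}, primary and secondary outcomes are assessed before and after the intervention. Under the retention item {18b} they are collected again at 3, 6 and 12 months. Baseline values of FIQ, VAS, PSQI and R-SCAS will therefore be available.

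The section Quantitative analysis under {20a} gives one inferential rule: "Differences between intervention and control groups will be tested using non-parametric tests". It adds that "continuous data will be presented using medians and interquartile ranges, whether they be normal or not" and that "A 5% level of significance will be used for all statistical tests". It names no test and does not mention baseline, a change score, a covariate or a model over visits. The item on additional analyses {20b} says "There will be no further analysis. The analyses carried out are described in the study".

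On losses, Sample size {14} says "Regarding the loss of participants, we will use the intent-to-treat purpose". The item whose heading covers both non-adherence and missing data {20c} says "In case of non-adherence of the participants, the intention-to-treat method will be used", and then defines this as analysing people in the group to which they were assigned. The planned size is given as "The sample will consist of 24 participants, divided into two groups, with 12 individuals each", without a power calculation.

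**The concern.** There are two linked weaknesses.

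The first is baseline. In a trial of 24 people, the baseline value of the primary outcome is usually the cheapest source of precision. The plan collects it but states no use for it in the comparison.

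The second is missing outcomes. Intention-to-treat answers the question of which arm a person counts in. It does not say what FIQ value stands for a person who left before the assessment. The plan offers it as the handling of loss and gives nothing else under the missing-data item. With no imputation and no likelihood-based model, a rank test at a visit can use only the people measured at that visit, which falls short of analysing everyone as randomised.

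Participation lasts about 15 months (3 months of intervention plus 12 of follow-up). The arms also differ in burden and contact: live group sessions against an e-book, and weekly calls to every control participant against calls to intervention participants only if needed. Unequal loss is possible, though the document gives no rate. At stake are precision that a small trial needs and the credibility of the intention-to-treat claim.

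**Working it through.** **Plan's own figure.** The only figure to reproduce is 2 × 12 = 24, which agrees. No effect size, SD, power, baseline correlation or dropout rate is stated, so everything below is in SD units with two-sided alpha 0.05. The correlation r and the losses are assumptions, shown as ranges.

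**1. Variance removed by baseline.** With baseline as covariate the residual variance is multiplied by 1 − r². For r = 0.5, 0.6, 0.7 this is 0.75, 0.64, 0.51, a reduction of 25%, 36% and 49%.

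**2. Detectable difference at 80% power (noncentral t).** Unadjusted: standard error √(2/n), df = 2n − 2. Adjusted: the same multiplied by √(1 − r²), df = 2n − 3.

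| Analysed per arm | Unadjusted | r = 0.5 | r = 0.6 | r = 0.7 |
|---|---|---|---|---|
| 12 | 1.20 SD | 1.04 | 0.96 | 0.86 |
| 10 | 1.33 SD | 1.15 | 1.06 | 0.95 |
| 9 | 1.41 SD | 1.22 | 1.13 | 1.01 |

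**3. Power by simulation.** Normal data, true effect 1 SD, 12 per arm, at least 3,000 simulated trials per cell. Repeat runs agree to within about two percentage points.

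| Method | r = 0.5 | r = 0.6 | r = 0.7 |
|---|---|---|---|
| Exact Mann-Whitney, post scores | 61% | 61% | 61% |
| Exact Mann-Whitney, change scores | 60% | 70% | 81% |
| Rank ANCOVA (Quade) | 71% | 77% | 83% |
| ANCOVA | 75% | 82% | 88% |

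All three rank methods fit the plan's wording. Against post scores, ANCOVA gains 14, 21 and 27 points. Against change scores it gains 15, 12 and 7. Against rank ANCOVA it gains 4, 5 and 5. At r = 0.3 the gain is small: 67% for ANCOVA against 61% for post scores.

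**4. Type I error.** With no true effect, and 9, 10 or 12 analysed per arm, the rank test on post scores rejected in 3.4% to 4.5% of simulated trials. There is no inflation.

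**5. Chance imbalance.** The baseline mean difference has SD √(2/12) = 0.408, so P(|difference| > 0.5 SD) = 2 × [1 − Φ(0.5/0.408)] = 0.22. This holds for any randomised trial with 12 per arm and is already reflected in the standard error of an unadjusted comparison.

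**6. Effect of loss on precision.** The 95% CI half-width for an unadjusted mean difference is t × √(2/n). At 12 per arm it is 2.074 × 0.408 = 0.85 SD. At 10 per arm, assuming two lost in each arm, it is 2.101 × 0.447 = 0.94 SD, about 11% wider. This is a t interval for means, used as a guide; the plan specifies no interval.

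**7. Text on missing values.** Sample size {14} ties intention-to-treat to loss of participants. Item {20c} defines it by assigned group and non-compliance. Neither says how a participant without a post-intervention or follow-up FIQ enters the test, and no other section does.

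**The case against.** The strongest reply is that the plan is silent, not wrong. It does not say that the tests are unadjusted. A rank test on change scores, or a rank ANCOVA, is also non-parametric, and the choice of test and covariates is often left to an analysis plan that is not shown. The {20b} sentence stands under a heading about subgroup and similar extra analyses, so it does not settle how the planned comparison uses baseline. Rank tests are defensible at 12 per arm and keep their type I error. The largest power gaps arise only on the post-score reading, and no correlation is given. Outcomes are collected by online form, separately from the meetings, and monthly messages support retention.

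Much of this stands. A reader might infer that baseline FIQ is definitely ignored and that dropouts will be deleted by rule. The documents do not say so: the first is read from silence, and the second is a consequence of having no missing-data method. A reader might also infer that chance imbalance biases the result. In a randomised comparison it does not; it costs precision.

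Two things remain. The missing-data item is answered, and answered with a principle that cannot do that job; this is a mismatch in the text, not an omitted detail. And {20b} does say that the analyses carried out are those described, so stating the use of baseline now is worthwhile.

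**Conclusion.** The point holds in this limited form. The plan states no use of baseline values that it already collects, and it presents intention-to-treat as the handling of loss and missing data, which it cannot be on its own.

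The cost in power depends on what the unnamed test turns out to be. For a 1 SD effect and r from 0.5 to 0.7, ANCOVA gains 14 to 27 points over a rank test on post scores, 7 to 15 over a rank test on change, and only 4 to 5 over rank ANCOVA. These figures assume normal data, 12 analysed per arm and the stated correlations.

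Attrition bias is possible but cannot be sized from the document. The matter is worth correcting before analysis; it does not invalidate the trial.

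**What to change.** In Quantitative analysis under {20a}, make the primary FIQ comparison baseline-adjusted at one named time point, for example the post-intervention assessment. Choose one of:

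- rank ANCOVA, if the team wishes to stay non-parametric;
- ANCOVA with baseline FIQ as covariate;
- a mixed model over visits with baseline FIQ as covariate and small-sample degrees of freedom.

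Report the adjusted difference with its 95% CI. Rank ANCOVA gives no difference on the FIQ scale, so take the estimate from ANCOVA in that case. Apply the same approach to VAS, PSQI and R-SCAS.

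In {20c}, keep intention-to-treat as the rule for arm assignment, and align the sentence in Sample size {14} with it. State separately how missing FIQ values are handled: either a likelihood-based model with baseline in the outcome vector, or multiple imputation. Both let all 24 randomised participants contribute, whereas a model with baseline only as covariate, used without imputation, drops anyone with no later visit. Add one sensitivity analysis with a defined unfavourable value for missing scores, such as the participant's own baseline FIQ or worse.

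No new participants, visits or measurements are needed. The cost is modest reliance on model assumptions and on data missing at random, which the sensitivity analysis probes, and a little more analysis work.
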